### Detailed structure of QI sessions

#### Session 1 (1 day)

a) Introduction: Why is QI necessary?

b) Short overview of the EQUIP programme

c) Review of the QI programme

d) Goals and methods of measurement

e) Healthcare as a system

f) Identification of potential deficiencies at each centre

g) Centre assignments and contact via Internet portal

#### Session 2 (1 day)

a) Repetition and reflection

b) Report on centre assignments

c) Improvement ideas

d) How to test new ideas

e) Implementation and requirements for sustained improvements

f) Homework (test and implement new ideas, internet portal)

#### Session 3 (1 day)

a) Repetition and review of activities during QI programme

b) Report of tests and results

c) Planning of new tests and/or implementation of successful test

### Control group centres

The centres that are randomised to the control group will receive a "low intensity" programme throughout the 10-month recruitment period. These centres will receive full training on the EQUIP protocol and database (telephone and internet training as for all centres) in addition to access to online reports which will enable them to assess their progress in management of ACS patients.

Regular telephone contact will be maintained with key staff at these centres to discuss general progress, resolve any queries and maintain enthusiasm.

### Patient enrolment

Daily screening of key wards and admission areas will identify potentially eligible patients as soon as possible after admission. All eligible patients will be enrolled into the study during the 10-month study period. Patients will be followed up until hospital discharge only to assess in-hospital treatments and investigations. If a patient is transferred to another hospital for continuing care and will be discharged from there, this transfer will be considered as discharge and staff will be asked to record the reason for transfer (e.g. patient transferred for coronary angiography). Centres will be asked to record data for all eligible patients. Using previous estimates of eligibility and enrolment, we estimate that centres may enrol 10-15 patients per month which translates into 4000-5000 patients in total over a 10-month period. The recruitment period will be approximately 10 months which includes a one-month run-in period, baseline phase (3 months), QI training phase (3 months) and QI implementation phase (3 months). Refer also to Figure 1.

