**Figure 1 F1:**
[figure not shown]
**Flow-diagram**.

#### Phase 1

Site selection and set-up phase. Potential centres will be identified by National Co-ordinators and invited to participate. 12 centres will be invited assuming a drop-out rate of 30% leaving on average 8 centres per country. Thus the expectation is that we will have 40 participating centres in total. Centres will then be informed about the study and ethical and regulatory documents obtained.

All participating centres will be provided with a full training programme on the EQUIP project and data collection tool using web-based and telephone training methods.

#### Phase 2

Run-in. Centres will enter a run-in phase for one month to ensure that they are able to collect data properly using the RIKS-HIA web-based system. An assessment of data quality and enthusiasm to participate will be made after this and those centres that are willing and able to continue will be invited to do so.

#### Phase 3

Baseline Phase. Centres will be randomised to either QI programme or control group. Centres will then collect data for 3 months as part of the baseline assessment of care.

#### Phase 4

QI programme (3 months). The main elements of the QI programme will be delivered over a period of 3 months (see **Quality Improvement phase**) during which time all centres will continue to collect data.

#### Phase 5

Centres will collect data for a further 3 months during which the QI centres will receive further input and feedback on performance.

#### Phase 6

Data cleaning, study close-out, statistical analyses and reports

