### Inclusion criteria

Patients with a good clinical history of ACS and at least one of the following:

a) New or transient ST or T wave changes on the ECG consistent with acute myocardial ischaemia

b) Elevation of troponin or other cardiac markers to levels indicative of myocardial necrosis according to local laboratory values

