### Randomisation

EQUIP-ACS has a cluster-randomised study design. Randomisation will be stratified by country and ability to perform percutaneous coronary intervention on-site. Centres will be randomised to the QI programme or not. The co-ordinating centre (CTEU) will inform centres at the beginning of the baseline phase of their randomised allocation. The rationale for this is that personnel at centres allocated to the QI training programme will require sufficient notification to ensure availability and secure travel arrangements for the meetings. There is a possibility that knowledge of the randomised allocation may influence practice patterns. However the influence of this potential bias can be tested by comparing treatment patterns across the two groups during the baseline data collection phase.

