### Statistical analysis plan

The primary outcome is a composite of 8 outcome measures. The proportion of outcomes fulfilled will be calculated on all patients for each time period and group. The change in the proportion over time (Δ = post QI - baseline) will be compared between groups.

Analysis of the primary outcome will be by hierarchical logistic regression to take account of the clustered nature of the data. For each patient up to 8 binary quality indicators will be recorded. The quality indicators are therefore nested within patient. Patients, in turn, are nested within centre. A three-level random effects model will be fitted with random effects for patient and centre. An indicator variable for time period (0 = baseline phase, 1 = post-QI phase) will be entered at level 2 (patient) as a fixed effect and an indicator variable for treatment group (0 = control, 1 = intervention) will be entered as a fixed effect at level 3 (centre). Other centre-level covariates that will be entered as fixed effects at level 3 are country and ability to perform PCI on site (since these will be stratification factors in the randomisation). The interaction between treatment indicator and time period will give a P-value and an estimate of the treatment effect expressed as an odds ratio for the probability of a quality indicator being fulfilled.

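### Patients are identified by staff who know their centre's arm, and the primary model has no patient case-mix term, so a post-programme shift in who is entered would bias the treatment effect

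*Protocol article*

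**What the plan says.** **Order of events.** Study phases, Phase 3: "Centres will be randomised to either QI programme or control group. Centres will then collect data for 3 months as part of the baseline assessment". The Randomisation section adds that the co-ordinating centre "will inform centres at the beginning of the baseline phase of their randomised allocation".

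**Who enters patients.** Patient enrolment: "Daily screening of key wards and admission areas will identify potentially eligible patients as soon as possible after admission", and "All eligible patients will be enrolled into the study during the 10-month study period". Data collection has participating centres enter the data.

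**Eligibility.** Inclusion criteria: "Patients with a good clinical history of ACS and at least one of the following". The two items that follow are ECG change consistent with ischaemia and raised troponin or other cardiac markers by local laboratory values.

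**Acknowledged bias.** Randomisation: "There is a possibility that knowledge of the randomised allocation may influence practice patterns". The section then says that "the influence of this potential bias can be tested by comparing treatment patterns across the two groups during the baseline data collection phase".

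**Primary model.** The Statistical analysis plan section sets out a three-level logistic model with random effects for patient and centre. Its fixed effects are period (the only one at patient level) and group, and "Other centre-level covariates that will be entered as fixed effects at level 3 are country and ability to perform PCI on site". The treatment effect is the group-by-period interaction, expressed as an odds ratio.

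**The concern.** In a cluster trial where patients are found after allocation is known, the arms can come to differ in who is entered as well as in how patients are treated. The outcome here is the proportion of indicators fulfilled among entered patients, so a change in the mix of entered patients moves it even if care does not change.

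Pressure on the measured indicators is also unequal. QI teams review their baseline results, plan weekly meetings and report continuously on the portal (Preliminary activities). In Phase 5 they receive further input and feedback. Control centres have online reports but not that programme. No deliberate omission is needed: team meetings could alter which wards are searched or how a good history is read. Fuller capture of poorly managed patients in QI centres would push the other way and hide a real benefit.

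At stake is whether a significant interaction, or its absence, can be read as being about care.

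**Working it through.** **1. The plan's own figures, used as benchmarks.** Table 1 reproduces if two-sided 5% and 80% power are assumed (neither is stated). The formula is (t_0.975,38 + t_0.80,38) × SD × √(2 × [1 + (m − 1) × ICC] / (20m)), with 38 = 2 × (20 − 1) degrees of freedom. For ICC 0.1 and m = 25: (2.024 + 0.851) × 0.9 × √(2 × 3.4 / 500) = 2.875 × 0.105 = 0.302, as printed. All ten rows agree to three decimals. The power table is not in question. The benchmarks are:
- minimum important difference: 10 points (0.5 on an average maximum score of 5);
- differences called detectable: 0.3 to 0.4 on that score, which is 6 to 8 points.

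**2. What the interaction removes.** The estimate is (QI post − QI baseline) − (control post − control baseline). If enrolment practice shifts an arm's proportion by the same amount b in both periods, b cancels. If it shifts QI centres by b in the post-QI period only, the estimate moves by b.

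**3. What the model could absorb.** Country and on-site PCI are constant within a centre. Period and group define the contrast itself. The patient random effect describes scatter between patients and does not correct a systematic change in their mix. No stated term takes up b.

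**4. Size of b.** Let entered patients have mean fulfilment a, and let a share f with mean a − g be left out of QI centres after the programme. The full-population mean is (1 − f)a + f(a − g) = a − fg, so b = f × g. This assumes no matching omission in controls and, on average, the same number of applicable indicators in omitted and entered patients. The documents give neither f nor g.

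| f | g (points) | b (points) | Score (5 × b) | Odds ratio if true fulfilment is 70% | Share of 10-point minimum |
|---|---|---|---|---|---|
| 5% | 10 | 0.5 | 0.025 | 1.02 | 5% |
| 10% | 20 | 2 | 0.10 | 1.10 | 20% |
| 20% | 20 | 4 | 0.20 | 1.22 | 40% |
| 20% | 30 | 6 | 0.30 | 1.36 | 60% |

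Odds ratio example: (0.74/0.26) / (0.70/0.30) = 1.22. The 70% is also assumed.

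**5. Effect on false positives.** A simulation with no true effect used 20 centres per group, 25 patients per centre per period, 5 indicators and 2,000 trials per setting. A centre-level t-test on the change stood in for the three-level model.

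| Omitted share | Log-odds gap | Bias (points) | Rejection rate |
|---|---|---|---|
| none | – | 0.0 | 5.7% |
| 10% | 1.0 | 1.9 | 13.6% |
| 20% | 1.0 | 3.9 | 39.7% |
| 20% | 1.5 | 6.1 | 69.9% |

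The variance components were assumed, and each centre's effect was held fixed across periods. Centre-by-period variation would lower these rates for the same bias. They show direction, not a forecast.

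**6. Would a shortfall be noticed?** The list described under Investigators covers enrolled patients only. The planning rate is 10 to 15 patients per centre per month, and the sample-size section says the exact rate is unknown. A centre falling from 15 to 12 a month (15 × 0.8) stays inside that range.

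**The case against.** The case for the plan is substantial.

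- **There are several safeguards.** A reader might infer that the baseline comparison is the only protection. It is not. Screening is daily and early, before discharge prescribing is known. All eligible patients are to be entered. Without a consent step there is no consent-driven selection. Investigators answer for data completeness and must allow access to source data. The interaction removes stable differences. These points stand. None of them counts eligible patients who were not entered.
- **Eligibility is not pure judgement.** ECG or marker evidence is also required, so discretion is bounded, though not removed.
- **The Randomisation section makes no false claim.** A reader might take it to say that the baseline comparison tests selective enrolment. The bias it names is early change in practice, and comparing baseline treatment patterns is relevant to that. It simply does not reach enrolment after the programme.
- **Part of the case mix is fixed by the measures.** Angiography, beta-blocker and ACE-inhibitor measures apply to defined subsets, and patients over 80 are excluded. This narrows the scope for bias, but by the protocol's own account risk stratification and statins apply to everyone.
- **Adjustment is no cure.** Covariates remove only shifts they measure. Leaving out a patient because treatment was poor, at the same case mix, would remain. Adjusting for stratification factors alone is also an accepted primary choice.
- **A full analysis plan may hold supporting analyses.** It may. The point rests on the primary model as the article states it.

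**Conclusion.** The point holds as a vulnerability of moderate weight. Allocation is known before any baseline or post-QI patient is identified, eligibility is partly judgement, and the stated model has no patient case-mix term. An enrolment shift that arises after the programme in one arm would therefore enter the treatment effect, upwards or downwards.

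Its size cannot be derived from the documents. Under the assumed inputs it runs from 0.5 points (5% omitted, 10-point gap) to 4 points (20%, 20-point gap). The latter is 40% of the minimum difference and 50% to 67% of the 6 to 8 points called detectable (4/8 and 4/6). Neither reaches those thresholds alone. Only the most extreme case tabulated, 6 points, meets the lower detectable figure.

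A reader might go further and conclude that QI centres will select patients, or that the result will be invalid. Nothing in the documents shows that differential entry is likely.

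**What to change.** 1. **Model.** Pre-specify patient-level (level 2) fixed effects for age, sex, diabetes, raised troponin, ST/T change, creatinine clearance and previous CABG, either in the primary model or as a key supporting analysis beside it. Leave out LVEF and documented risk score, because the programme may change whether they are recorded.
2. **Reporting.** Tabulate patients entered per centre per month, and the same admission characteristics, by arm and phase. This compares each arm with its own baseline rather than with a wide planning range.
3. **Limits.** State that adjustment removes only measured case-mix shifts, and that adding covariates slightly changes the conditional odds ratio being estimated.
4. **Randomisation section.** Keep the text. Add a sentence that the baseline comparison addresses early practice change and does not test selective enrolment in the post-QI phase.

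The cost is analysis wording and one table from the existing database. Five of the seven characteristics are already needed for the angiography measure, and age for the exclusion criterion. Sex is assumed to be recorded. No extra visits, staff or audit are required.

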### Data collection

Information about eligible patients will be entered onto the EQUIP-ACS database, which has been adapted from the RIKS-HIA database to include translations into local language and some modifications or additions to fields. The database has a facility to generate online reports which allows centres to assess their progress. The RIKS-HIA data collection tool is a validated web-based system with 10 years of experience [27,28]. All data will be entered in an anonymous manner at the participating centres and transferred in an encrypted format to the main server at UCR, Uppsala where it will be held securely. All data management will take place at UCR.

### Centre training

Before the start of the study, centres will receive training from CTEU and UCR. Centres will be trained on the EQUIP data collection tool using a web-based system and telephone training. The CTEU will provide training and ensure that centres fully understand the protocol and procedures of the study.

### Ethical and regulatory issues

This study is a QI initiative and therefore can be considered part of routine professional activity and education. Except for an increased compliance to accepted standards and professional guidelines, no change to routine health care is expected as part of this study. Ethics Committee Approval has been obtained in each of the 5 countries and for all participating centres for the study to be conducted without obtaining written informed consent from patients. Approvals for data to be transferred from the admission institution to UCR have been obtained from the appropriate local and national authorities. The study will be conducted in accordance with Good Clinical Practice guidelines [32] and the Declaration of Helsinki [33]. Permission and support of local hospital management will be obtained and will be an essential part of the success of this programme. Since this study is not evaluating any specific pharmacological treatment or medical device it falls outside the European Clinical Trials Directive and does not require formal pharmacovigilance.

### Sample size and statistical considerations

The primary outcome is based on the 8 quality improvement variables. Two of the variables will be available in all patients (risk stratification and statin use) whereas the others will be available in a proportion of the whole group. We can document the use of treatments as a proportion at a centre level or at the level of the patient we can score each variable as 1 (administered) or 0 (not administered), allowing a maximum score of 8 for each patient. For the sample size calculation it appeared more straightforward to use the scoring system. Some patients will not contribute to the final analysis as they may not be considered for 5 of the outcome measures. Using a pragmatic assumption we estimate that the average "maximum" score per patient will be 5, allowing for the fact that a proportion will not contribute to the final analysis. To calculate the sample size we have taken the possible differences in score using simulated individual level patient data corrected for centre effect (i.e. that patterns of practice in a particular centre will have similarities across patients treated at that centre and therefore results from each patient cannot be regarded as "independent"). If the maximum score is estimated at 5 each one point would equate approximately to a 20% absolute difference in the frequency of use of that treatment at a centre level. We estimate that a 10% absolute difference would be considered reasonable "minimum" difference to demonstrate that the QI programme can change practice. This equates to an absolute average difference of about 0.5 between the QI centres and control.

In PROMIS-UK [31] we found that a difference of 0.3 between the education group and control group was just detectable with a p value of 0.05, with a total of 1000 patients and 38 centres. The inter-cluster correlation coefficient (ICC) for the control arm of PROMIS was 0.10026.

The sample size estimate for EQUIP uses the following formula:(1)

Where "N_cluster_" and "N_simple_" are the sample sizes for cluster randomisation and simple randomisation respectively. "m" is the number of patients per cluster (i.e. per hospital) and "ICC" is the inter-cluster correlation coefficient.

The table below shows the detectable differences in scores between groups using an ICC of 0.1 or 0.2 and 40 or 50 patients per centre.

Table 1 shows that the study is well powered in the post QI phase to detect differences of about 0.4 with 800 patients assuming an ICC of 0.2. Our anticipated total enrolment over the whole period (baseline, during the QI phase and post QI phase is expected to be a minimum of 2000 and a maximum of 4000, We believe the main "power" of the study will lie in the post QI phase and a total enrolment of 1000 patients (500 per group) will give us good power to detect differences of 0.3-0.4 which equates to absolute differences in rates of use of treatments of 6-8%, Since our minimum clinically important difference is 10%, the study can be considered "well powered". Centres will be asked to recruit all non-ST elevation ACS patients but we do not know the exact enrolment rate in the centres that will take part hence the need to identify a range of sample size estimations. However as this is largely driven by the number of centres it is important we have 40 participating centres.

**Table 1 T1:** Sample size calculation based on score of drug use at discharge

ICC	Centres per Group	Patients per Centre	Patients per Group	SD	Detectable Difference
0.1	20	20	400	0.9	0.312
0.1	20	25	500	0.9	0.302
0.1	20	30	600	0.9	0.295
0.1	20	40	800	0.9	0.286
0.1	20	50	1,000	0.9	0.281
					
0.2	20	20	400	0.9	0.401
0.2	20	25	500	0.9	0.394
0.2	20	30	600	0.9	0.390
0.2	20	40	800	0.9	0.384
0.2	20	50	1,000	0.9	0.380

It was not felt appropriate to use the estimated differences between baseline data and post QI data in the sample size estimation as too many assumptions needed to be made. Therefore we feel we have made a "conservative" sample size estimation that should allow a good opportunity to detect realistic differences between the two groups.

### Statistical analysis plan

The primary outcome is a composite of 8 outcome measures. The proportion of outcomes fulfilled will be calculated on all patients for each time period and group. The change in the proportion over time (Δ = post QI - baseline) will be compared between groups.

Analysis of the primary outcome will be by hierarchical logistic regression to take account of the clustered nature of the data. For each patient up to 8 binary quality indicators will be recorded. The quality indicators are therefore nested within patient. Patients, in turn, are nested within centre. A three-level random effects model will be fitted with random effects for patient and centre. An indicator variable for time period (0 = baseline phase, 1 = post-QI phase) will be entered at level 2 (patient) as a fixed effect and an indicator variable for treatment group (0 = control, 1 = intervention) will be entered as a fixed effect at level 3 (centre). Other centre-level covariates that will be entered as fixed effects at level 3 are country and ability to perform PCI on site (since these will be stratification factors in the randomisation). The interaction between treatment indicator and time period will give a P-value and an estimate of the treatment effect expressed as an odds ratio for the probability of a quality indicator being fulfilled.

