**Methods/Design:**

This will be a multi-centre cluster-randomised study in 5 European countries: France, Spain, Poland, Italy and the UK. Thirty eight hospitals will be randomised to receive a quality improvement programme or no quality improvement programme. Centres will enter data for all eligible non-ST segment elevation acute coronary syndrome patients admitted to their hospital for a period of approximately 10 months onto the study database and the sample size is estimated at 2,000-4,000 patients. The primary outcome is a composite of eight measures to assess aggregate potential for improvement in the management and treatment of this patient population (risk stratification, early coronary angiography, anticoagulation, beta-blockers, statins, ACE-inhibitors, clopidogrel as a loading dose and at discharge). After the quality improvement programme, each of the eight measures will be compared between the two groups, correcting for cluster effect.

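### The primary model has no centre-by-period random effect, so its treatment-by-period test keeps 5% only if all centres in an arm shift alike

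*Protocol article*

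**What the plan says.** The Randomisation section states that "EQUIP-ACS has a cluster-randomised study design". The Statistical analysis plan section then sets out the primary model term by term:

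- Purpose: "Analysis of the primary outcome will be by hierarchical logistic regression to take account of the clustered nature of the data".
- Random part: "A three-level random effects model will be fitted with random effects for patient and centre", with quality indicators nested in patients and patients nested in centres.
- Period (baseline or post-QI): "will be entered at level 2 (patient) as a fixed effect".
- Treatment group: a fixed effect at centre level.
- Stratification factors: "Other centre-level covariates that will be entered as fixed effects at level 3 are country and ability to perform PCI on site".
- Test and estimate: "The interaction between treatment indicator and time period will give a P-value and an estimate of the treatment effect expressed as an odds ratio".

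No section mentions a period effect that varies by centre. Under Patient enrolment, patients are followed only to hospital discharge, so the baseline and post-QI phases consist of different admissions.

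**The concern.** The quantity tested is the difference between arms in the average change of a centre from baseline to post-QI. A centre intercept that is the same in both periods drops out of each centre's change. The patient effect is independent from one patient to the next, so it cannot carry a shift shared by all patients of one centre in one period. Country and on-site PCI enter as main effects and absorb no change over time. The error left for the interaction is therefore patient-level and indicator-level, although the centre was randomised.

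If some hospitals move up and others down between the two phases for reasons unrelated to the programme, the model counts that movement as if it were backed by independent patients. At stake are the level of the single primary test and the width of its confidence interval. The error can only run towards false claims of effect, and it grows with the ICC and with the number of patients per centre.

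**Working it through.** **1. The plan's own figures.** Table 1 (20 centres per group, SD 0.9) reproduces in all ten rows with

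difference = 0.9 × √(2 × [1 + (m − 1) × ICC] / (20m)) × (t₀.₉₇₅,₃₈ + t₀.₈₀,₃₈).

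Two-sided 5% and 80% power are inferred; the text does not state them. For ICC 0.1 and m = 25: 0.9 × √(2 × 3.4 / 500) × 2.875 = 0.302, as printed. Table 1 concerns the post-QI comparison alone. It is used here only to confirm the planning inputs.

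**2. Inputs for the interaction test.**
- ICC: 0.1 and 0.2, the planning values. The earlier UK trial's control arm gave 0.10026.
- Centres: K = 40, as in Table 1. The Abstract says 38; with K = 38 the percentages below are the same to one decimal.
- Patients per centre per period, m: the minimum enrolment of 2,000 over three phases gives 2,000 / (3 × 40) ≈ 17. The 1,000 patients cited for the post-QI phase give 1,000 / 40 = 25. Equal numbers at baseline are assumed.
- r, the correlation between a centre's underlying levels in the two periods: not in the document, so it is varied.

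**3. Formulas** (linear scale, total variance 1, balanced).
- True variance of a centre's change: V = 2 × [(1 − r) × ICC + (1 − ICC)/m].
- Variance used by a model with one centre intercept: M = 2s²/m. Here s² is the pooled residual variance: s² = {2K(m − 1)(1 − ICC) + (K − 2)[(1 − ICC) + m(1 − r)ICC]} / {2K(m − 1) + K − 2}.
- Actual type I error of a nominal 5% test: 2 × [1 − Φ(1.96 / √(V/M))].

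**4. One case in full:** ICC 0.1, m = 25, r = 0.8.
- V = 2 × (0.02 + 0.036) = 0.112.
- s² = (1,920 × 0.9 + 38 × 1.4) / 1,958 = 0.9097, so M = 2 × 0.9097 / 25 = 0.0728.
- √(V/M) = 1.24, and the error is 2 × [1 − Φ(1.58)] = 11.4%.

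**5. Range.**

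| ICC | m | r = 1 | 0.95 | 0.9 | 0.8 | 0.7 |
|---|---|---|---|---|---|---|
| 0.1 | 17 | 5.0% | 6.1% | 7.1% | 9.3% | 11.4% |
| 0.1 | 25 | 5.0% | 6.6% | 8.2% | 11.4% | 14.5% |
| 0.2 | 25 | 5.0% | 8.6% | 12.2% | 18.6% | 23.9% |

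**6. Checks by simulation under the null.** The linear analogue agrees with the table within simulation error, and a t-test on centre-level changes stayed at about 4% to 6%. A second simulation generated binary indicators from a logistic model (38 centres, m = 25, assumed total latent centre variance 0.5) and tested them with a linear random-intercept equivalent. It rejected in 5.5%, 10.8%, 15.2% and 20.4% of trials at r = 1, 0.95, 0.9 and 0.8, while the centre-level test stayed at 4.8% to 5.4%. These rates exceed the ICC 0.1 rows because that latent variance implies a different ICC on the patient proportion. The direction is stable; the size depends on the scale.

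**7. What valid inference costs.** With z in place of t and 80% power, the detectable difference in change is 0.9 × √(V × 2/20) × 2.80. At m = 25 and r = 0.8 this is 0.267 at ICC 0.1, against 0.215 if M replaces V. At ICC 0.2 it is 0.303 against 0.204. Both valid figures are below the difference of about 0.5 that the protocol takes as its minimum.

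**The case against.** The strongest reply is that the harm is conditional. At r = 1 the test is valid, and the article gives no r. That stands. A reader might infer that the primary test has been shown to exceed 5%; the document does not support this. It reports that use of evidence-based treatments tends to rise over time anyway, and that clopidogrel use rose in the control centres of the Swedish study. That is evidence of a background trend, not of a trend that differs between hospitals. The two phases also come from the same hospitals, with one three-month phase between them.

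It is tempting to cite the QI teams' locally chosen changes as proof of drift. That is variation in the programme's effect within one arm. It bears on the confidence interval but cannot inflate type I error when the programme does nothing.

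The figures are a linear stand-in; the planned three-level logistic model was not fitted. The ICC comes from a five-drug score in another trial, and 0.2 is a planning scenario. This limits the precision of the sizes, not the structural point.

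A reader might also infer that Table 1 contradicts the analysis. It does not: the sample size section discloses that baseline-to-post change was deliberately left out of the sizing. Nor is the lack of detail on degrees of freedom or robust variances a fault in a journal article. The random-effects structure, however, is stated and not left open.

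**Conclusion.** The point holds in conditional form. As written, the primary model protects its interaction test against stable differences between centres but not against centre-specific change between periods. The nominal 5% is right only if centres in an arm shift identically. With r between 0.95 and 0.7, type I error is roughly 6% to 11% at ICC 0.1 with 17 patients per centre per period, 7% to 14% with 25, and 9% to 24% at ICC 0.2 with 25. These figures rest on an assumed r, equal cluster sizes, the planning ICCs and a linear approximation. The direction does not depend on those choices: any r below 1 makes the P-value too small and the interval too narrow. Nothing else in the article repairs this.

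**What to change.** Add a random centre-by-period effect (a centre-level random effect for the period indicator) to the primary model. Base inference on the number of centres, for example through small-sample degrees of freedom, or with a centre-level analysis of change as a sensitivity check.

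The cost is one extra variance component and a change of wording before analysis; no new data are needed. The interval becomes somewhat wider: at ICC 0.1, m = 25 and r = 0.8 the standard error rises by a factor of about 1.24. If r is in fact 1, little is lost. With about 40 centres the added variance will be estimated imprecisely and inference from the logistic model stays approximate, which is the reason for the centre-level check.
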